### 16.3 Secondary

The following definitions are used for the secondary endpoints of interest:

• Response rate at 3 months post radiation treatment: is reported as a proportion calculated as the number of cases with complete response (CR) or a partial response (PR) at 3-month post radiation imaging based on Lugano criteria divided by the total number of treated patients. Treated patients who do not have a 3-month evaluation will be classified as a non-response.

• Local control rate at 2-years: defined from the time of registration to local relapse that overlaps the treated site (95% isodose line).

• Patient Reported Outcomes/Quality of life: FACIT-Fatigue given as SOC for Lymphoma patients within 3 months after end of radiation treatment will be used as outlined in section 4.0 and 7.0.

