16.6.2 Secondary Analyses

16.6.2.1 Response Rate: All patients who were registered to the study and started treatment will be included in the response rate analysis. Response rate will be defined as the proportion of patients displaying response (PR or CR) at 3 months post treatment; patients who did not have a 3-month post treatment assessment will be considered a non-response. A chi-square test will be used to compare response rates between the two treatment arms. Absolute risk difference and relative risk will be calculated; 95% confidence intervals will be calculated using the score method.

16.6.2.2 Local control: All patients who were registered to the study and started treatment will be included in the local control analysis. A local recurrence event is any event defined as disease relapse occurring in the area treated before with radiation (anything included within the 95% isodose line). The local control interval will be defined as the number of days from end of radiation treatment until first local recurrence within 24 months post radiation treatment; censoring will occur at date of patient death or date of last disease evaluation (based on imaging and clinical exam). Local control rates will be estimated separately for the two treatment groups at 3-, 6-, 12-, 18, and 24-months post radiation treatment using the Kaplan-Meier method. Hazard ratio and 95% confidence interval for comparison of local recurrence between the two treatment arms will be estimated from a Cox proportional hazards model.

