16.6.2.5 Exploratory Analyses

Financial toxicity: COST-FACIT with added questions to assess specifically for travel and accommodation expenses, travel distance and time, and loss of work time for patient and care givers scores will be assessed at end of treatment and described separately for the two groups. The financial toxicity score will be calculated using items FT1-FT11 where items FT2, FT3, FT4, FT5, FT8, FT9, and FT10 will first need to be reverse scored by subtracting the response from 4 and then sum the individual items to obtain a score. Then multiply the sum of the item scores by the number of items in the scale (11) and divide by the number of items the patient answered. The financial toxicity score ranges from 0-44 where a higher score indicated better financial well-being. The financial toxicity score will be summarized separately for the two treatment groups with the mean, standard deviation, median, 25^th^ percentile, and 75^th^ percentile. No comparison between treatment groups will be conducted. Individual items will be described with mean, standard deviation.

Financial health care expenditure will be determined by first obtaining base cost rates from Mayo Clinic’s reimbursement database for all codes included in the planning, treatment, and management of patient’s enrolled in both arms. Mean total radiotherapy costs will then be calculated using inflation adjusted standardized Medicare rates and summarized separately for the 2 treatment arms; a linear regression model will be used to estimate the difference in Financial health care expenditure between the two treatment arms.

Biopsies of enrolled patients will be evaluated for pathological assessment of cellular and genetic mutations. This includes: TP53 alteration by FISH and expression of TP53, MYC and proliferation index (Ki-67) by immunohistochemistry stain (IHC).

Baseline PET/CT scan of patients will be sent to MIMvista to undergo autosegmentation to calculate the MTV, TLG and SUVmax of their disease.

Multivariable models will be used to evaluate associations of these biomarkers separately with local control (logistic regression) and response (Cox proportional hazards). Models will include biomarker, treatment arm as a covariate along with potentially confounding variables.

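### The exploratory biomarker models are swapped: logistic regression is assigned to censored local control and Cox regression to yes/no 3-month response

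*Protocol*

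**What the plan says.** Section 16.6.2.5 plans multivariable models that relate each biomarker (TP53, MYC and Ki-67 from tissue; MTV, TLG and SUVmax from baseline PET/CT) to two outcomes, adjusting for arm and possible confounders. It pairs outcomes and models as "local control (logistic regression) and response (Cox proportional hazards".

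The same two outcomes are defined a few paragraphs earlier.

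- Local control, Section 16.6.2.2: "The local control interval will be defined as the number of days from end of radiation treatment until first local recurrence within 24 months", and "censoring will occur at date of patient death or date of last disease evaluation (based on imaging and clinical exam". Rates come from Kaplan-Meier, and "Hazard ratio and 95% confidence interval for comparison of local recurrence between the two treatment arms will be estimated from a Cox proportional hazards model".
- Response, Section 16.6.2.1: "Response rate will be defined as the proportion of patients displaying response (PR or CR) at 3 months post treatment", and "patients who did not have a 3-month post treatment assessment will be considered a non-response". For the arms, "A chi-square test will be used to compare response rates between the two treatment arms".

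Section 16.3 also treats local control as a time to event but starts the clock elsewhere: "defined from the time of registration to local relapse that overlaps the treated site (95% isodose line".

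**The concern.** Each outcome gets one class of model for the arm comparison and the opposite class for the biomarker analysis. Nothing explains the change, so the two model names look transposed.

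For local control, a logistic model needs a known status at a fixed time. The protocol defines no such binary outcome and gives no rule for patients whose follow-up ends early. Incomplete follow-up is plausible:

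- Section 3.1 admits any stage and relapsed or refractory disease.
- Section 1.0 notes that relapse after radiation alone is mostly outside the irradiated area.
- Section 13.3 moves patients with progressive disease to event monitoring, and the key events named for that phase in Section 4.0 do not include local relapse.
- Section 4.0 leaves later follow-up assessments to the clinician.

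For response, a Cox model needs an event time and a censoring rule, and the protocol gives neither.

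At stake is the only regression plan for the prognostic work named in Sections 1.0, 2.4 and 16.1.

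**Working it through.** The protocol states no figure for these models, so there is none to reproduce. The check has two parts.

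**1. Outcome against model**

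| Outcome | Type as defined | Censoring | Arm comparison | Biomarker model (16.6.2.5) |
|---|---|---|---|---|
| Local control (16.6.2.2) | days to first local recurrence | at death or last evaluation | Kaplan-Meier, Cox | logistic |
| Response (16.6.2.1) | PR or CR at 3 months, yes/no | none; missing is non-response | chi-square | Cox |

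The last column is reversed relative to the second and third. No section defines a time to response or a fixed-time binary version of local control. If scan date were used as the event time for response, the hazard ratio would partly reflect scheduling within the ±14-day window of Section 4.0. Patients set to non-response because they had no 3-month assessment have no assessment time at all.

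**2. What a binary 24-month outcome does under censoring**

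Inputs:
- The example 2-year local control rates in Section 16.5.1.1, 94.1% and 87.1%, give true risks of 5.9% and 12.9%. They are borrowed here as the risks in a low-risk and a high-risk biomarker group.
- The proportion censored by 24 months is not given. It is assumed to be 10% to 40%.
- Recurrence and censoring times are simulated as independent exponentials, 2,000,000 draws per scenario.

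The true odds ratio is (0.129/0.871) / (0.059/0.941) = 0.1481/0.0627 = 2.36.

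| Censored by 24 months | Counted as controlled: risks | Odds ratio | Dropped: risks | Odds ratio |
|---|---|---|---|---|
| 10% | 5.63%, 12.25% | 2.34 | 6.23%, 13.52% | 2.35 |
| 20% | 5.28%, 11.56% | 2.34 | 6.56%, 14.22% | 2.36 |
| 30% | 4.95%, 10.89% | 2.35 | 6.98%, 15.16% | 2.38 |
| 40% | 4.62%, 10.16% | 2.33 | 7.58%, 16.27% | 2.37 |

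Each odds ratio is [p2/(1−p2)] / [p1/(1−p1)]. At 40%, counted as controlled, it is (0.1016/0.8984) / (0.0462/0.9538) = 0.1131/0.0484 = 2.33. So absolute risks move in opposite directions under the two rules, but the association barely moves when both groups are censored equally.

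The same table shows what happens when censoring depends on the biomarker. Suppose 10% are censored in the low-risk group and 40% in the high-risk group:
- Counted as controlled: (0.1016/0.8984) / (0.0563/0.9437) = 0.1131/0.0597 = 1.90.
- Dropped: (0.1627/0.8373) / (0.0623/0.9377) = 0.1943/0.0664 = 2.92.

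Against a true 2.36, the answer then depends on a handling rule that the protocol does not state. The 10% versus 40% split is an illustration, not a prediction.

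For scale, at the example rates about 51 × 0.059 + 51 × 0.129 = 3.0 + 6.6 = 9.6 local recurrences are expected among 102 patients, so the classification of a few censored patients could matter.

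**The case against.** The strongest case for leaving this alone is that it is harmless. The models are listed as correlative in Section 2.4 and exploratory in Section 16.4. No decision rule, sample size or stopping rule uses them. Tissue is optional and used only if enough remains. The correct definitions stand nearby, so a statistician would probably notice the slip. All of this stands, and it sets the grade of the point. It does not make the sentence right: an analysis plan that follows it carries the error forward, and one that corrects it contradicts the protocol.

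A second defence is technical. Logistic regression for local control is acceptable if 24-month status is known for nearly everyone, and a Cox model with the same time for every patient can serve as a device for estimating a risk ratio. The protocol sets up neither. It allows censoring before 24 months and defines no time for response.

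A reader might infer the stronger claim that both sets of biomarker estimates would be invalid. For local control this is not shown: with censoring unrelated to the biomarker, the odds ratio stays between 2.33 and 2.38 against a true 2.36. What is shown is distorted absolute risk, loss of information, and possible bias if censoring is related to the biomarker. Nor do the documents support treating these models as half of the trial's purpose. The primary goal is acute toxicity, and the secondary goals in Section 2.2 contain no biomarker.

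Sparse events are a separate matter. They would trouble either model, and the choice of covariates may properly be left to the analysis plan.

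**Conclusion.** The point holds. The model assignment in Section 16.6.2.5 contradicts Sections 16.6.2.1 and 16.6.2.2 and is most likely a transposition. The response half is the clearer error, because the Cox model has no event time to work with. The local-control half is a mismatch whose effect depends on follow-up. It is nil with complete 24-month status, confined mainly to absolute risks and precision if censoring is unrelated to the biomarker, and a possible bias in the association otherwise. The figures rest on an assumed censoring range, exponential times, and arm-level example rates borrowed for biomarker groups.

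Only the exploratory biomarker analyses are affected; the primary and secondary comparisons between arms use suitable methods. It is a should-fix correction.

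**What to change.** In Section 16.6.2.5, swap the two model names: Cox proportional hazards regression for local control, and logistic regression for response at 3 months.

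State that the local-control model uses the time origin and censoring of Section 16.6.2.2, and that response uses the definition in Section 16.6.2.1, including missing as non-response. Before that, reconcile the local-control origin, which is registration in Section 16.3 and end of radiation in Section 16.6.2.2.

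The cost is one corrected sentence plus the alignment of one definition. It needs no new data and no change to sample size, visits or the primary analysis.

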### 16.7 Data and Safety Monitoring

#### 16.7.1 Safety Review

The principal investigators and the study statistician will review the study monthly to identify accrual, adverse event, and any endpoint problems that might be developing. The Mayo Clinic Comprehensive Cancer Center (MCCCC) Data Safety Monitoring Board (DSMB) is responsible for reviewing accrual and safety data for this trial at least biannually, based on reports provided by the MCCCC Statistical Office.

#### 16.7.2 Adverse Event Stopping Rules

The stopping rules specified below are based on knowledge available at study development. We note that the Adverse Event Stopping Rule may be adjusted in the event of either (1) the study re-opening to accrual or (2) at any time during the conduct of the trial and in consideration of newly acquired information regarding the adverse event profile of the treatment(s) under investigation. The study team may choose to suspend accrual because of unexpected adverse event profiles that have not crossed the specified rule below.

Accrual will be temporarily suspended if at any time we observe events considered at least possibly related to study treatment (i.e., an adverse event with attribute specified as “possible,” “probable,” or “definite”) that satisfy one of the following:

• If 4 or more patients in the first 10 treated patients (per each treatment regimen; 1. 10 Gy in 5 fractions, 2. 8 Gy in 2 fractions, 3. 9 Gy in 3 fractions, 4. 24 Gy in 12 fractions (i.e., SOC)) experience a grade 3 or higher adverse event, at least possibly related to treatment at any time following completion of the protocol treatment within 90 days post-treatment.

• After the first 10 patients have been treated (per treatment arm): if ≥ 40% of all patients experience a grade 3 or higher adverse event, at least possibly related to treatment following the completion of protocol treatment to 90 days post-treatment.

We note that we will review grade 4 and 5 adverse events deemed “unrelated” or “unlikely to be related”, to verify their attribution and to monitor the emergence of a previously unrecognized treatment-related adverse event.

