### 6.2 Randomization Procedures

#### 6.2.1 The factors defined in **Section 5.0** will be used as stratification factors.

#### 6.2.2 After the patient has been registered into the study, the values of the stratification factors will be recorded, and the patient will be assigned to one of the following treatment groups using the Pocock and Simon dynamic allocation procedure, which balances the marginal distributions of the stratification factors between the treatment groups (Pocock and Simon 1975).

- Arm 1: The prescription dose will be 9 Gy delivered in 3 fractions of 3 Gy per fraction or 8 Gy delivered in 2 fractions of 4 Gy per fraction . In some cases, the investigator can use 10 Gy delivered in 5 fractions (stomach/orbit/other at treating MD’s discretion).
- Arm 2: The prescription dose will be 24 Gy delivered in 12 fractions of 2 Gy per fraction.

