## **8.0 Dosage Modification Based on Adverse Events**

Aside from early stopping rules (below), dose modification might be adopted if the hypofractionation regimen was associated with increased adverse events in the first 10 accrued patients. Specifically, the experimental arm will be monitored, after 10 patients are treated per arm, for less than 40% of patients experiencing a grade 3+ adverse event possibly related to treatment within 90 days post-treatment. If that threshold is crossed, the study will temporarily be suspended, and the experimental arm will be adapted to 10 Gy in 5 fractions.

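### The 16.7.2 stopping rule counts severe toxicity only after radiotherapy is completed, and Section 8.0 does not say when its own count starts

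*Protocol*

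**What the plan says.** Protocol 16.7.2 has two numeric triggers for temporary suspension of accrual, both for grade 3 or higher events at least possibly related to treatment.

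- Bullet 1 works per regimen (10 Gy in 5, 8 Gy in 2, 9 Gy in 3, 24 Gy in 12). It acts at 4 or more of the first 10 treated patients, with events counted "at any time following completion of the protocol treatment within 90 days post-treatment".
- Bullet 2 works per arm after the first 10 patients. It acts "if ≥ 40% of all patients experience a grade 3 or higher adverse event", with events counted "following the completion of protocol treatment to 90 days post-treatment".

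Section 8.0 adds a rule for one arm only: "the experimental arm will be monitored, after 10 patients are treated per arm". The condition that it watches is worded "for less than 40% of patients experiencing a grade 3+ adverse event possibly related to treatment within 90 days post-treatment". The consequence is "If that threshold is crossed, the study will temporarily be suspended, and the experimental arm will be adapted to 10 Gy in 5 fractions". That regimen is already permitted inside the arm; 6.2.2 says "In some cases, the investigator can use 10 Gy delivered in 5 fractions".

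On-treatment toxicity is collected. Section 7.2.1 has the clinical team contact patients weekly during treatment, and 10.2.1.1 requires adverse event reporting from registration. The footer to the Section 4.0 schedule puts radiotherapy at 5 days for 3 fractions and 16 days for 12, give or take 2 days.

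**The concern.** A stopping rule for radiation toxicity would be expected to start its clock at the first fraction. As written, both 16.7.2 bullets start it at the end of treatment. A patient whose related grade 3 event appears and settles before the last fraction adds to the denominator but not to the numerator.

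The gap is longest in the 24 Gy arm, where the course is about three times as long and 8.0 does not apply. In the experimental arm the two sections can disagree: an event confined to treatment is excluded by 16.7.2, while nothing in 8.0 excludes it.

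These are the protocol's only numeric safety triggers, and 8.0 also bears on which regimen later experimental patients receive. What is at stake is a delayed or missed suspension, and doubt about which rule governs. The primary comparison is not involved.

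**Working it through.** **Consistency of the thresholds.** The protocol states no operating characteristics for these rules, so there is no such figure to reproduce. The two 16.7.2 bullets agree where they meet: 4/10 = 40%. Section 8.0, taken word for word, names the complement (below 40%, that is 3 or fewer of 10).

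**The windows side by side.**

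| Rule | Unit | Start of count | End of count |
|---|---|---|---|
| 16.7.2 bullet 1 | regimen | completion of treatment | 90 days post-treatment |
| 16.7.2 bullet 2 | arm | completion of treatment | 90 days post-treatment |
| 8.0 | experimental arm | not stated | 90 days post-treatment |

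The lead-in to 16.7.2 refers to events seen at any time, but those events must then satisfy one of the bullets, so the bullets set the window.

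**Length of the uncounted period** (durations from Section 4.0), as a share of the time from first fraction to 90 days post-treatment:

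- 24 Gy in 12: 16/(16 + 90) = 16/106 = 15%.
- 9 Gy in 3: 5/(5 + 90) = 5/95 = 5%.

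These are shares of time. They do not say what share of events falls in the gap.

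**A concrete case.** Four of the first 10 patients on a regimen have a related grade 3 event, and one of these events resolves before the last fraction. Bullet 1 counts 3/10 and accrual continues. Counted from the first fraction it would be 4/10 and accrual would be suspended.

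**Illustration under assumptions.** Let r be the true rate of related grade 3+ events and s the share of affected patients whose events occur only during treatment. Neither is in the protocol. Bullet 1 then trips with probability P(X ≥ 4), where X is binomial with n = 10 and p = r(1 − s), that is, 1 minus the sum over k = 0 to 3 of C(10,k) p^k (1 − p)^(10−k).

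| r | s = 0 | s = 5% | s = 15% | s = 25% |
|---|---|---|---|---|
| 40% | 0.618 | 0.566 | 0.459 | 0.350 |
| 20% | 0.121 | 0.104 | 0.074 | 0.050 |
| 10% | 0.013 | 0.011 | 0.007 | 0.005 |

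For r = 40% the values of p are 0.40, 0.38, 0.34 and 0.30. The window matters in absolute terms only if severe toxicity is near the rule's own threshold. At a 10% rate the rule almost never trips under either definition.

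**The 8.0 switch.** Suppose 4 of 5 patients on 10 Gy in 5 have events and 0 of 5 on the other experimental regimens. The arm is at (4 + 0)/(5 + 5) = 40%, and 8.0 names 10 Gy in 5 as the destination. If those four events fall after treatment, bullet 1 of 16.7.2 has also been met for 10 Gy in 5 itself (4 events, with fewer than 10 patients treated), so accrual is suspended on that regimen's own signal.

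**The case against.** The case against giving this much weight is substantial.

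First, a reader might infer that severe toxicity during radiotherapy is never counted or goes unwatched. The documents do not support that. The exclusion is explicit only in 16.7.2; 8.0 sets no start, so it can be read to count on-treatment events in the experimental arm. Section 16.7.2 also says "The study team may choose to suspend accrual because of unexpected adverse event profiles that have not crossed the specified rule below", and it allows the rule itself to be adjusted during the trial. Section 16.7.1 provides monthly review by the principal investigators and statistician and DSMB review at least biannually. Related grade 3 events and all grade 4 and 5 events are reported within 24 hours, although 10.2.2.3 exempts common grade 3 radiation effects that do not lead to hospitalization. An event still present after the last fraction counts. All of this stands, but none of it supplies a numeric trigger for on-treatment events in the control arm or aligns the two sections.

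Second, a reader might infer that 8.0 suspends the trial when toxicity is low. It does not mean that. Its opening refers to increased adverse events, it acts when the threshold is crossed, and 16.7.2 gives the direction correctly. This is a wording slip with recoverable intent.

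Third, a reader might infer that 8.0 obliges the trial to move every later experimental patient onto a regimen that has just proved toxic. That rests on silence. Section 8.0 opens permissively, saying that modification might follow, and ties it to the hypofractionation regimen, a description that the title and Section 1.0 attach to 9 Gy in 3. Section 16.7.2 monitors 10 Gy in 5 separately. The scenario also needs heavy early use of a regimen allowed only in some cases. What remains is a small ambiguity, because the later sentence of 8.0 speaks of the whole arm in firmer terms.

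Fourth, the 40% row of the illustration exceeds even the grade 2+ rates assumed in 16.5.4 (31% and 10%). That is fair. The row shows how the rule behaves at its own threshold and does not forecast this trial.

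**Conclusion.** The window point holds. Both bullets of 16.7.2 exclude related grade 3+ events that start and resolve during treatment, about 5 days for 3 fractions and about 16 days for 12, and 8.0 leaves its start undefined. The two rules can therefore count the same event differently. This follows from the text and needs no assumption.

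The size of the effect cannot be determined from the protocol. The probabilities above depend on an assumed grade 3+ rate and an assumed share of events confined to treatment. They range from a negligible change at a 10% rate to a fall from 0.62 to between 0.57 and 0.35 at a 40% rate.

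The threshold phrase in 8.0 is a wording correction, and the 10 Gy in 5 question is a minor clarification. The sample size and the primary chi-squared test are unaffected. Overall, this is a safety-rule definition worth correcting at the next amendment. It is not a flaw in the trial's main inference.

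**What to change.** In both bullets of 16.7.2 and in 8.0, define countable events as grade 3 or higher, at least possibly related, with onset from the first fraction to 90 days post-treatment.

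In the same amendment:

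- In 8.0, state the trigger as 40% or more (4 or more of the first 10), matching 16.7.2.
- In 8.0, say that the move to 10 Gy in 5 fractions applies only when that regimen does not itself account for the crossing, and that otherwise the suspension stays in place pending review by the investigators and the DSMB.

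The cost is amendment wording. No extra patients, visits or data are needed, because toxicity is already assessed weekly on treatment and reported from registration. The one operational consequence is that a suspension becomes slightly more likely, or comes slightly earlier, once on-treatment events count.
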